#### **5.4 Adverse Event Reporting and Documentation**

An “Adverse Event” will be defined as any adverse change from the subject’s pre-treatment baseline condition, including any clinical or laboratory test abnormality that occurs during the course of research after treatment has started. Adverse events will be categorized and graded in accordance with the NCI CTC (Version 3.0).

A “Serious Adverse Event” will be defined as an undesirable sign, symptom or medical condition which 1) is fatal or life threatening; 2) requires inpatient hospitalization or a prolongation of existing hospitalization; 3) results in persistent or significant disability/incapacity; 4) constitutes a congenital anomaly or a birth defect and/or; 5) medically significant such that it may jeopardize the subject, and may require medical or surgical intervention to prevent one of the outcomes listed above.

A summary of all adverse events (not just those considered related to the vaccine) will be kept which will categorize the event by organ system, relationship to treatment, its grade of severity, and resolution. The PI will periodically review the collective adverse events with the intention of identifying any trends or patterns in toxicity. If any such trends are identified, depending on their severity and frequency, a protocol amendment will be considered.

All adverse events which are serious and unexpected should be reported immediately to [name] ([contact]) or his designee [contact]) and to the FDA. Fatal or life-threatening, unexpected adverse events will be reported to the FDA by telephone, facsimile, or in writing as soon as possible, but no later than 7 calendar days after first knowledge by the sponsor followed by as complete a report as possible within 8 additional calendar days. Serious, unexpected adverse events that are

not fatal or life-threatening will be reported to the FDA by telephone, facsimile, or in writing as soon as possible, but no later than 15 calendar days after first knowledge by the sponsor.

All adverse events that are considered serious, unanticipated, and related or possibly related to the research (as defined by 21CFR312.32[a]) will be reported to the Duke University Medical Center IRB using the appropriate SAE report form. At the time of the annual progress report to the Duke University Medical Center IRB, a summary of the overall toxicity experience will be provided.

## **6 DATA AND SPECIMEN COLLECTION**

### **6.1 Pretreatment Evaluation**

#### **6.1.1 Baseline and Eligibility**

To be enrolled, patients must undergo leukapheresis. Clinical and laboratory evaluations will be obtained within 2 weeks of enrollment for the purposes of meeting Inclusion and Exclusion Criteria as outlined in the Study Flow Sheet.

Pathology slides consisting of 1 H&E and 19 unstained slides, from all prior resections or biopsies, prepared on Fischer Plus glass or Histostix coated slides when available will be mailed to:

[name]., Ph.D.  
[name]  
[name]  
Duke University Medical Center  
[name]

Blood samples will also be sent for the following study related tests: T4/T8 ratio (Lab Code 2500202) and, ABC (Lab Code 2010200) with manual differential (Lab Code 2000640).

Initial clinical evaluations will also include a complete physical, ophthalmologic and neurologic examination with KPS rating, MMSE testing, and Curran rating.

A baseline and study eligibility MRI (with and without gadolinium enhancement) of the brain using standard 5 mm slices with 2.5 mm spacing for comparison to subsequent MRI images will also be obtained.

Patients will also be assessed before vaccine # 1 and every 4 months after vaccine # 3 by a panel of clinical laboratory analyses to screen for the development of autoimmunity. The most common manifestations of autoimmunity seen in related trials (Phan, Yang et al. 2003; Attia, Phan et al. 2005; Blansfield, Beck et al. 2005; Jaber, Cowen et al. 2006) have included enterocolitis, dermatitis, uveitis, hepatitis, and hypophysitis. Laboratory evaluations to detect subclinical disease will be obtained as follows: serum thyroglobulin Ab (Lab Code 1802105), rheumatoid factor (Lab Code 5560195), antinuclear Ab (Lab Code 5560214) (Homma, Sagawa et al. 2006); human anti-human (anti idiotypic) Ab ([name] Lab), erythrocyte sedimentation rate (Lab Code 2000860), thyroid-stimulating hormone (Lab Code 1802085), ACTH (Lab Code 1800020), cortisol (Lab Code 1802010), free T4 (Lab Code 1802081), ALT, and AST (Lab Code 1004000). Finally, if cerebrospinal fluid becomes available, it will be checked for oligoclonal banding (Lab Code 1543440).

## **6.2 Data and Specimens to be Accessioned**

### **6.2.1 During Temozolomide**

Patients will have a T4/T8 ratio (Lab Code 2500202) and ABC with manual differential (Lab Code 200640) approximately weekly during TMZ administration during radiation. During cycles of TMZ, the laboratory tests will be obtained prior to each next cycle and at the time of vaccination (Day 21  $\pm$  2).

### **6.2.2 Prior to Initial Leukapheresis**

After patients have been enrolled, and before leukapheresis, a ProTRAK form will be submitted to the Cancer Center Protocol office. All enrolled patients will then undergo a leukapheresis for baseline immunological monitoring. Prior to leukapheresis, patients will have blood samples taken for the following tests as required by the Duke Apheresis Center: OP8 (Lab Code 1004500) and  $\beta$ -HCG (Lab Code 1800440). Total estimated blood volume required for these evaluations is 10 cc. For patients without sufficient venous access for leukapheresis, a temporary intravenous catheter may be inserted. To prevent the development of hypocalcemia from the citrate used for leukapheresis, all patients will be given oral Tums, 2 tablets, b.i.d for 2 days prior to the leukapheresis procedure. Patients who have lowered levels of calcium will be treated per Apheresis lab standard protocols under the direction of [name], M.D. All leukaphereses will be 2 to 4-hours long, and it is estimated that 1.5 to 3 times the blood volume (~10-12 L) will be processed during all leukaphereses.

### **6.2.3 Prior to Immunizations**

Prior to the first immunization, DTH skin tests (Tjoa, Simmons et al. 1998; Lodge, Jones et al. 2000) will be administered and assessed as outlined in Standard Operating Procedure (SOP-JHS-HDC-CL-014 "Delayed-Type Hypersensitivity Test Procedure"). Responses will be assessed and recorded on the appropriate form (FORM-JHS-HDC-CL-014C "Delayed-Type Hypersensitivity Test Form"). An additional leukapheresis will be required for any patients who have a positive DTH skin test for PEPvIII for immunologic monitoring.

### **6.2.4 During and After Immunizations**

- Clinical evaluations with each vaccine or leukapheresis will include a general physical, neurologic, and ophthalmologic examination, KPS, and MMSE.
- Radiographic evaluations consisting of a contrast enhanced brain CT or MRI scan will be obtained every 8  $\pm$  4 weeks.
- Blood will be obtained for T4/T8 ratio (Lab Code 2500202), ABC (Lab Code 2010200) with manual differential (Lab Code 2000640), serum for PEPvIII-KLH ELISA ([name] Lab), and 10 yellow ACD (9 mL), 3 red (9 mL), and 1 purple (3 mL) tubes for Immunologic Monitoring *prior* to vaccination #1 and with each vaccination after vaccination #3. Blood will also be obtained for

sub-clinical autoimmunity prior to vaccine # 1 and every 4 months after vaccine # 3. Estimated volume of blood for these tests is 120 cc.

- During TMZ cycles, ABC (Lab Code 2010200) with manual differential (Lab Code 2000640) will be monitored at the time of vaccination (day  $21 \pm 2$ ) and before the next TMZ dosing of each 4 week cycle.
- DTH testing will occur with the fourth vaccination (SOP-JHS-HDC-CL-014 “Delayed Type Hypersensitivity Testing Procedure”). Results will be read and recorded on the appropriate form (FORM-JHS-HDC-CL-014C “Delayed Type Hypersensitivity Testing Form”)  $48 \pm 24$  hours later. An additional leukapheresis will be required for any patients who have a positive DTH skin test for PEPvIII for immunologic monitoring.

## **7 CLINICAL RESPONSE EVALUATIONS AND STATISTICS**

### **7.1 Radiographic Response and Progression Criteria for Patients with Residual Disease**

Residual disease will be defined as contiguous contrast enhancement  $> 1\text{ cm} \times 1\text{ cm}$  in each of two perpendicular planes. For residual disease present at the time of the last MRI prior to initiating vaccine treatment, radiographic response will be evaluated based on the NCI-endorsed, World Health Organization RECIST criteria and using a modified version of the MacDonald criteria (Macdonald, Cascino et al. 1990; Galanis, Buckner et al. 2006) which is outlined below.

#### **7.1.1 Complete Response**

Complete disappearance of enhancing tumor on consecutive CT or MRI images at least 1 month apart, and neurologically stable or improved and at the same or a lower steroid dose. To be assigned a status of “Complete Response” as a best overall response, changes in tumor measurements must be confirmed by repeat assessments that should be performed no less than 4 weeks after the criteria for response is first met.

#### **7.1.2 Partial Response**

At least a 30% reduction in longest diameter on an axial image of any enhancing tumor on consecutive CT or MRI images at least 1 month apart, and neurologically stable or improved and at the same or a lower steroid dose. To be assigned a status of “Partial Response” as a best overall response, changes in tumor measurements must be confirmed by repeat assessments that should be performed no less than 4 weeks after the criteria for response is first met taking as a reference the first post-radiation scan.

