#### **7.1.3 Stable Disease**

Insufficient change to qualify for Partial Response or Progressive disease.

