#### **7.1.4 Progressive Disease**

At least a 25% increase in the longest diameter on an axial image of any enhancing tumor that is  $> 1\text{ cm}$  in each of 2 perpendicular planes on consecutive CT or MRI images or the appearance of a new radiographically demonstrable lesion that measures  $1\text{ cm}$  or greater in each of two perpendicular axial planes taking as a reference the first post-operative or first post-radiation scan whichever is most recent.

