## **7.2 Special Circumstances**

- **If a scan is suspicious but not definitive for progressive disease (including indeterminate lesion size or enhancement that is not clearly disease progression) in the absence of clinical progression, an investigator may elect to confirm progression through alternate means, including PET scan, biopsy, repeat MRI at 4 weeks, symptomatic follow up or other modalities.**
  - Protocol treatment will continue until the investigator considers progression documented.
- **Disease that was measurable at baseline and appeared to be one solid mass splits to become 2 or more smaller lesions**
  - note that the lesion has split, to identify the separate lesions as unique and to record the measurements of each.
  - appearance of these individual split lesions will not automate a response assignment of PD; they will contribute to a determination of progression only if the sum of all lesions meets the criteria for PD.
- **2 or more lesions which were distinctly separate at baseline become confluent at subsequent visits**
  - note the occurrence and capture the required measurement(s) of the confluent mass.
- **A required region of a baseline scan may be unavailable or technically inadequate, and 1 or more lesions are detected on a subsequent scans.**
  - Such lesions are identified as additional evaluable lesions that do not contribute to determination of that visit's response.
  - If at a successive time point disease progression is noted, the overall response per time point will be PD.
  - For those areas inadequate at baseline, the first scan available will become the reference scan by which later scans are compared for evaluable progression.
- **1 or more lesions are detected in regions unavailable or inadequate at baseline that were also not required**
  - regarded as new lesions, resulting in an overall response of PD for that time point.
- **Regions are not available or adequate at post-baseline visit assessments that showed disease at baseline**
  - an overall response of NA will be assigned to that visit unless other available data shows progression.

| Overall Response | Measurable Lesions                                                                    | Evaluable Lesions | New Lesions | Overall neurological status             | Steroid Use               | Additional notes                                                                                                 |

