|-------------------------|----------------------------------------------------------------------------------------------|--------------------------|--------------------|------------------------------------------------|----------------------------------|-------------------------------------------------------------------------------------------------------------------------|
| PD               | PD                                                                                    | PD                | Yes         | Unequivocal worsening                   | Stable or increased use   | PD by any single component (not steroids by criteria) no sooner than 1 month after the first course of treatment |
| SD               | All other combinations, but please note the following particular combinations: |                          |                    |                                                |                                  |                                                                                                                         |
|                         | CR, PR or SD                                                                          | CR or SD          | No          | NA                                      | Off steroids, stable dose | Note that a lack of steroid or neurological information could prevent CR or PR from being recorded               |
|                         | CR, PR or SD                                                                          | CR or SD          | No          | improved, unchanged, possible worsening | NA                        | Note that a lack of steroid or neurological information could prevent CR or PR from being recorded               |
|                         | NA                                                                                    | NA                | NA          | improved, unchanged, possible worsening | Off steroids, stable use  |                                                                                                                         |

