|                         | CR, PR or SD                                                                          | CR or SD          | No          | improved, unchanged, possible worsening | Off steroids, stable dose | A CR or PR overall response assignment is not possible with a neurological grading of -1.                        |
| PR               | PR or CR                                                                              | CR or SD          | No          | unchanged or improved                   | Off steroids, stable use  | All conditions need to apply and CR criteria do not apply.                                                       |
| CR               | CR                                                                                    | CR                | No          | unchanged or improved                   | Off steroids              | All conditions need to apply.                                                                                    |
| NA               | NA                                                                                    | NA                | NA          | NA                                      | Off steroids, stable dose | NA applies when NA is true of both radiology and neurological status.                                            |

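### Section 7.1.2 lets a 30% fall in any one enhancing lesion count as partial response without a fall in the sum, and 7.2 gives confluent lesions no reference measurement

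*Protocol*

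**What the plan says.** Section 7.1.2 grants PR for "At least a 30% reduction in longest diameter on an axial image of any enhancing tumor". The change must appear on consecutive images and be confirmed, with conditions on neurological status and steroid dose. Section 7.1.4 uses the same unit for progressive disease (PD): "At least a 25% increase in the longest diameter on an axial image of any enhancing tumor", or a new lesion of sufficient size. Stable disease (SD) in 7.1.3 is what remains: "Insufficient change to qualify for Partial Response or Progressive disease". None of the three mentions a sum or target lesions.

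Section 7.2 brings in a sum once. When one baseline mass splits, the pieces are recorded as separate lesions and "they will contribute to a determination of progression only if the sum of all lesions meets the criteria for PD". When lesions that were separate at baseline run together, the instruction is only to "note the occurrence and capture the required measurement(s) of the confluent mass".

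The overall-response table in 7.2 puts PD first, with the note "PD by any single component (not steroids by criteria) no sooner than 1 month after the first course of treatment". Its PR row carries the note "All conditions need to apply and CR criteria do not apply".

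**The concern.** The word 'any' works in opposite directions in the two definitions. For PD it is cautious, because one growing lesion is enough. For PR it is permissive, because one shrinking lesion is enough whatever the others do, short of PD. Section 7.2 recognises for progression that the pieces of a split lesion must be added together, but does not carry this over to response. A patient could therefore be counted as a responder with no reduction in total measured diameter.

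For confluent lesions the difficulty is a gap. The protocol asks for a measurement and does not say what to compare it with, so two readers could both follow the text and score the same scan differently.

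At stake are the exploratory clinical-response analyses in Sections 8 and 10.3 and, for confluent lesions only, radiographic time to progression (TTP) in 7.3.

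**Working it through.** The protocol states no figure to reproduce. Inputs from the protocol are the PR threshold of -30% (7.1.2), the PD threshold of +25% (7.1.4), the sum rule for split lesions (7.2), and the precedence of PD in the table (7.2). All lesion sizes below are assumptions chosen for illustration, and the confirmation, neurological and steroid conditions are taken as met. Percentage change = follow-up / reference - 1.

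**1. Two lesions, main lesion growing by less than 25%.**
- Small lesion: 1.0/1.5 - 1 = -33.3%, which meets 7.1.2.
- Main lesion: 4.8/4.0 - 1 = +20.0%, below the PD threshold.
- Sum: (1.0 + 4.8)/(1.5 + 4.0) - 1 = 5.8/5.5 - 1 = +5.5%.
- Literal 7.1.2: PR. On the sum: SD.

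**2. Same small lesion, main lesion growing by 25% or more.**
- Main lesion: 5.2/4.0 - 1 = +30.0%, which meets 7.1.4.
- 7.1.2 and 7.1.4 are both met, and the table resolves this to PD. The false PR does not arise.

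**3. One baseline lesion that splits.**
- 4.0 cm becomes 2.0 + 2.0 cm. Each piece: 2.0/4.0 - 1 = -50%. Sum: 4.0/4.0 - 1 = 0%.
- Literal 7.1.2: PR. The sum rule in 7.2 gives no PD and is silent on response.
- 4.0 cm becomes 2.6 + 2.6 cm. Each piece: 2.6/4.0 - 1 = -35%. Sum: 5.2/4.0 - 1 = +30%. Here 7.2 gives PD, which prevails over the literal PR.

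**4. Stable lesions that become confluent, under the two possible comparators.**

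| Lesions and geometry | Against the larger former lesion | Against the sum |
|---|---|---|
| 2.0 + 2.0 cm, end to end, 4.0 cm | 4.0/2.0 - 1 = +100% | 0% |
| 4.0 + 1.5 cm, end to end, 5.5 cm | 5.5/4.0 - 1 = +37.5% | 0% |
| 4.0 + 0.9 cm, end to end, 4.9 cm | 4.9/4.0 - 1 = +22.5% | 0% |

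Two 4 x 1 cm lesions joining side by side form a 4 x 2 cm mass. Treating the shapes as rectangles, the longest diameter goes from √17 = 4.12 to √20 = 4.47 cm, or +8.5% against either lesion. Against a single former lesion the first two rows of the table pass +25%; the third row and the side-by-side case do not.

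**The case against.** The best defence of the text has four parts.

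*'Any enhancing tumor' may mean whatever enhancing tumour is present.* Section 7.1 says response is based on RECIST and modified MacDonald criteria, so the single-lesion reading is not the only one. This stands as a statement of ambiguity, but nothing in 7.1.2 selects the total, and the table does not say how to combine a lesion at -33% with one at +20%.

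*The overall-response table protects against a false PR.* It does so once a component reaches PD. A reader might infer that a patient can be PR however much the main tumour grows. The documents do not support that, because growth of 25% or more is PD. Below that limit the table does not help.

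*Mergers.* A reader might infer that the protocol scores stable lesions that merge as progression. It does not. Section 7.2 names no comparator and attaches no outcome, whereas elsewhere in the same list it says so when PD follows. A reader might also infer that such a scan would end vaccination, since vaccines run until progression. That does not follow either. For suspicious but indefinite scans 7.2 allows confirmation by other means, and "Protocol treatment will continue until the investigator considers progression documented".

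*Reach.* Multicentric disease is excluded (4.2.1), the primary endpoint is regulatory T-cell function, response rate is not a listed objective, and 10.3 treats TTP as hypothesis-generating. PR rather than SD does not move the TTP date, because 7.1.4 takes a post-operative or post-radiation scan as its reference. All of this stands and keeps the point minor. The exclusion does not remove it: 7.2 itself provides for separate baseline lesions, and a split needs only one.

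**Conclusion.** The point holds as a minor defect in an endpoint definition. As worded, 7.1.2 can classify a patient as PR when the sum of diameters is unchanged or slightly larger, either because a small lesion shrinks while the main one grows by less than 25%, or because one lesion splits. In the examples the sum changes by +5.5% and 0%.

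For confluent lesions the finding is only that the reference measurement is missing. If 7.1.4 is applied against a single former lesion, a merger of stable lesions may be read as progression, depending on size and geometry.

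The conclusion rests on a literal reading of 'any' and on assumed lesion sizes. The documents give no frequency of multiple or split lesions. The number affected among the 20 to 26 patients is likely to be small and could be zero. Only exploratory response and, through the merger gap, exploratory TTP are touched.

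**What to change.** In 7.1.2, define PR as at least a 30% reduction in the sum of the longest diameters of all measurable enhancing lesions, counting the pieces of a split lesion, against the same sum on the reference scan. The other PR conditions stay as they are.

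For confluent lesions, reconcile 7.1.4 and 7.2 by stating which reference measurement the confluent mass is compared with when the endpoint is scored. This concerns endpoint scoring only; it proposes no change to when treatment continues or stops.

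The cost is two sentences. The longest diameters are already needed for 7.1 and 7.2, so no new measurement is required. The downside is slightly fewer partial responses among patients with several or split lesions.
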